### Adverse events and data safety and monitoring

An adverse event refers to an untoward occurrence during the study, which may or may not be causally related to the intervention [32]. We will collect information relating to adverse events from randomisation until the participant completes the 12 month post-operative assessment.

Serious adverse events (SAE) are those which result in death, are immediately life-threatening, rehospitalisation, result in persistent or significant disability or incapacity, or have important clinical sequelae. Serious adverse events will be reported to the organisation’s Human Research Ethics Committee. All adverse events will be reviewed on a monthly basis by senior surgeons in the organisation’s orthopaedic department. Senior surgeons will consider the likely contribution of tourniquet use towards each complication and recommend to the investigators whether to modify or cease the study based on their findings. The surgeon whose patient had the adverse event will be excluded from the final decision making regarding whether the event is related to tourniquet use. Annual reports of the study’s progress will be sent to the organisation’s Human Research Ethics Committee.

### Statistical analysis plan

The main results will be based on intention-to-treat analysis which will include all participants as randomised. Per protocol analysis will also be conducted as secondary analysis and include only patients whose surgery was completed as randomised. All categorical data will be summarised using frequencies and percentages and baseline characteristics will be compared using the Chi-squared statistic. Interval or continuous data will be summarised using means with standard deviations or medians with lower and upper quartiles if the data are skewed. The amount of missing data for each group and each outcome will be described with frequencies and proportions. Analysis will include cases with available data. No imputation of missing data will occur. For questionnaire data, if a participant has not responded to ≥15% of questions in a questionnaire (or subscale where relevant), the responses for that scale will not be included in the analysis.

Linear mixed models [33] will be used for group comparisons of quadriceps strength at the different follow-up time points (2 days, 5 days, 3 months and 12 months). The major advantages of using this method are that it accounts for intra-individual correlations in observations, multiple variables can be included in the model and the method uses all available data even in the presence of unbalanced data. If assumptions permit, the restricted maximum likelihood approach will be adopted. The models will include an interaction term between time and treatment group, which will indicate the between group differences in quadriceps strength changes from baseline. The linear mixed model will also be considered for the analysis of continuous secondary outcomes that are available at multiple follow-up time points (> 3 time points). Other continuous outcomes that are only assessed at baseline and once/twice at follow-up will be analysed using linear regression, allowing for estimation of clustered sandwich error estimates [34]. Non-parametric models such as quantile regression will be considered for cases where assumptions of linear models are not satisfied.

Secondary outcomes that are categorical will be analysed using logistic regression models [35]. Count data such as hospital length of stay will be analysed using Poisson regression or other count-data models (e.g. negative binomial regression) if the assumptions of the Poisson regression models are not satisfied [36].

Questionnaire data will be analysed as a total score for the OKS, or component score for the WOMAC (Pain, Stiffness and Function), KSS (Knee Score and Function Score) and EQ-5D-5 L (descriptive system and VAS).

To explore the relationship between quadriceps strength and patient function, strength will be correlated with patient reported outcomes using Pearson’s correlation coefficient [37].

Relevant tests will be two-sided and considered significant if *p* values are less than 0.05. Stata Statistical Software version 14 or later or R Statistical Packages version 3 or higher will be used for analysis.

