### Objectives

The primary objective of this study is to determine whether non-tourniquet use during TKR reduces quadriceps strength less than tourniquet use when measured three months post-operatively.

A secondary objective is to determine whether non-tourniquet use during TKR reduces quadriceps strength less than tourniquet use at day 2 and 5, and 12 months post-operatively.

Other secondary objectives are to determine the effects of tourniquet use on:Pain and analgesia requirementsSelf-reported physical function and quality of lifeBlood loss and replacementSurgeon satisfaction with the intra-operative visual fieldOperation and anaesthetic timeComplications including revision surgeryCement mantle qualityPatient satisfactionHospital length of stay

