### Outcome measures and assessment time points

The primary outcome is the maximum percentage change in isometric quadriceps strength assessed preoperatively and 3 months following TKR. Strength will be measured in Newtons and assessed using a fixed-base electromechanical dynamometer (IsoForceControl EVO2 dynamometer [20]) with the knee stabilised in 60 degrees of flexion. Patient will be seated in a customised chair with a frame that fixes the dynamometer in position. The force plate will be applied adjacent to the malleoli of the ankle. Following 1–2 practices, participants will extend their knee as forcefully as they can for 10 s. The maximum force from three consecutive attempts will be recorded. Fixed-based dynamometer has very good to excellent reliability in people following arthroplasty [21].

Quadriceps strength at day 2 and 5, and 12 months post-operatively are secondary outcomes. Other secondary outcomes include:Post-operative inpatient pain and analgesia requirementsKnee pain intensity on day 2 and 5 post-operatively according to a 0–10 numeric scale (0 = no pain, 10 = extreme pain)Morphine equivalent daily dose [22] (mg, average for first 5 days)Blood loss and replacementIntra-operative blood loss (ml, sucker bottle minus irrigation volume)Transfusion (units)Surgeon satisfaction with intra-operative visual field1–10 numeric scale (1 = completely unsatisfied, 10 = completely satisfied)Operation and anaesthetic time (minutes)Complications during inpatient stayDVT or PEWound complications such as infection, haematoma or breakdown which require a change in management such as antibiotics or reoperationMedical complications (Medical Emergency Team (MET) calls [23] or death)Hospital length of stay (days)Self-reported pain, physical function and quality of life at 3 and 12 monthsKnee Society Score (KSS) [24]Oxford Knee Score (OKS) [25]WOMAC [26]EQ-5D-5 L [27]Revision surgery within 12 monthsCement mantle quality at 12 months [28]Patient satisfaction at 3 and 12 months

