### Sample size

The sample size was calculated on the basis of the primary outcome. To the best of the our knowledge, at the time of study development there was no published data reporting quadriceps strength following tourniquet use and total knee replacement that could be used to estimate a sample size for this study. Therefore, allowing for a medium to large effect size (Cohen’s d = 0.65), based on the large quadriceps function differences between groups observed by Liu et al. [16] which were measured using surface electromyography, a two-sided significance level of α = .05 and power of 80%, a minimum sample size of 39 participants per arm was estimated. Allowing for a 15% drop-out rate, we aimed to recruit 45 participants to each group.

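### The time-by-group interaction measures change from baseline only if baseline is the reference level of time; one baseline-adjusted 3-month contrast would be a clearer and more precise primary test

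*Protocol article*

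**What the plan says.** The Objectives section sets one primary question: whether surgery without a tourniquet "reduces quadriceps strength less than tourniquet use when measured three months post-operatively". The outcomes section defines the endpoint: "The primary outcome is the maximum percentage change in isometric quadriceps strength assessed preoperatively and 3 months following TKR". It also ranks the other visits: "Quadriceps strength at day 2 and 5, and 12 months post-operatively are secondary outcomes".

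The Statistical analysis plan section assigns linear mixed models to "group comparisons of quadriceps strength at the different follow-up time points (2 days, 5 days, 3 months and 12 months"). The models are to include an "interaction term between time and treatment group, which will indicate the between group differences in quadriceps strength changes from baseline". On the significance rule it says: "Relevant tests will be two-sided and considered significant if *p* values are less than 0.05".

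Table 1 shows strength measured before surgery as well as at all four follow-ups. The section does not say whether the pre-operative value is a level of time, a covariate, or already subtracted from the response. It does not single out the 3-month contrast as the primary test.

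**The concern.** The visit list contains only follow-ups, yet the interaction over time is described as a difference in change from baseline. Both statements hold if baseline is an additional, reference level of time. If the listed visits are all the levels, the description is wrong, because each interaction coefficient is then measured against the reference follow-up.

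A second difficulty does not depend on the coding. A four- or five-visit model has several interaction coefficients, and the text speaks of a single term. An analyst who reports the overall interaction test would be testing all visits together, whereas the objective concerns 3 months only. A result driven by day 2 or by 12 months could then be read as an answer to the primary question, or a steady deficit could be missed.

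**Working it through.** **1. The plan's own figure.** Inputs from the Sample size section: d = 0.65, two-sided 0.05, power 80%.
- Normal approximation: n per arm = 2 × (1.960 + 0.842)² / 0.65² = 37.2, rounded up to 38.
- Two-sample t-test: 38.14, rounded up to the stated 39.

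The stated size is reproduced. It is the size for one two-group comparison at one time point, which is the contrast recommended below.

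**2. What the 3-month interaction coefficient estimates.** Let d(t) be the true group difference at time t, with d(baseline) = 0 by randomisation.
- Baseline as reference level: coefficient = d(3 months) − d(baseline) = d(3 months).
- Four follow-ups only, day 2 as reference: coefficient = d(3 months) − d(day 2). Using change scores as the response does not alter this, because the baseline value cancels.
- Four follow-ups only, group main effect plus 3-month interaction: d(day 2) + [d(3 months) − d(day 2)] = d(3 months).

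So the model can deliver the right quantity under any coding. What matters is which term is read.

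Assumed effect patterns, in SD units (none is given in the protocol):

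| Day 2, day 5, 3 months, 12 months | True 3-month effect | Coefficient, baseline as reference | Coefficient, day 2 as reference |
|---|---|---|---|
| −0.65, −0.65, −0.65, −0.65 | −0.65 | −0.65 | 0 |
| −1.3, −1.0, −0.65, −0.3 | −0.65 | −0.65 | +0.65 |
| −0.65, −0.65, 0, 0 | 0 | 0 | +0.65 |
| 0, 0, 0, −0.65 | 0 | 0 | 0 |

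A restricted maximum likelihood fit to one simulated dataset confirmed the first coding. The 3-month coefficient was −0.475, equal to the directly calculated difference in change.

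**3. The joint test.** This was a simulation of 2000 runs with 39 per arm, an assumed correlation of 0.5 between all visits and unit SDs. The table gives the share of runs with p < 0.05 when the true 3-month effect is zero:

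| Pattern | Joint test, baseline included (4 df) | Joint test, follow-ups only (3 df) | 3-month coefficient, baseline as reference |
|---|---|---|---|
| Effect at 12 months only | 83% | 84% | 4.5% |
| Effect at days 2 and 5 only | 95% | 93% | 5.7% |

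The joint tests correctly detect that something differs somewhere, but they do not address 3 months. The single coefficient stays near its nominal level.

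**4. Gain from baseline adjustment.** Let r be the correlation between baseline and 3-month strength, with equal SDs σ.
- Variance of a change score: 2σ²(1 − r).
- Residual variance after adjusting for baseline: σ²(1 − r²).
- Ratio: (1 + r)/2. The standard error ratio is its square root.

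| Assumed r | Variance ratio | SE ratio | Reduction in SE |
|---|---|---|---|
| 0.3 | 0.65 | 0.806 | 19% |
| 0.5 | 0.75 | 0.866 | 13% |
| 0.7 | 0.85 | 0.922 | 8% |

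With unequal SDs s0 and s3, the change-score variance minus the adjusted variance is (s0 − r·s3)², which is never negative. Apart from the one degree of freedom spent on the slope, adjustment does not lose precision.

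**The case against.** The strongest reply is that the text is sound on its natural reading. The list gives the visits at which groups are compared, and nobody would test a group effect before surgery, so leaving baseline off that list is to be expected. The phrase about change from baseline suggests that baseline is in the model, and the data exist. The same section applies clustered standard errors to other outcomes measured at baseline and once or twice afterwards, which hints that baseline is stacked as a repeated record. No joint test is mentioned. The objectives, the outcome definition and the sample size all point to one 3-month comparison. A condensed article may leave parameterisation to a fuller analysis plan.

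Most of this stands. A reader might infer that baseline is excluded, that the trial therefore has little power for its primary question, or that its type I error is inflated. The protocol supports none of these. Loss of power would require that baseline be left out, that day 2 be the reference, that this coefficient alone be tested and that a particular day-2 deficit exist. Inflated error would require a common residual variance and unequal visit SDs, neither of which is specified.

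Two things remain. The sentence about the interaction is true under one coding and false under another that the preceding list permits. And a change-from-baseline interaction, even when correctly coded, is less precise than a baseline-adjusted contrast from the same data. Adjusting by covariate is one of several valid ways to use baseline, but it is correct whichever reading was meant.

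**Conclusion.** The point holds as an improvement, not as a must-fix error. The description of the interaction depends on a coding that the text does not state, and an overall interaction test would not isolate 3 months under any coding. The model class is suitable and the sample size is not in question.

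The gain is a standard error about 8% to 19% smaller than that of a plain change-from-baseline contrast. This rests on assumed correlations of 0.7 to 0.3, equal SDs, and strength analysed in the same units at both times. The size of the gain on a percentage-change scale cannot be derived from the protocol. The effect patterns and the simulated rejection rates illustrate the mechanism and are not forecasts for this trial.

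A linked point belongs in the same edit. The outcome is a percentage change, whereas the model is described for strength itself. On the raw scale the interaction estimates a difference in Newtons.

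**What to change.** In the Statistical analysis plan section:

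- State that the primary test is the model-based group difference at 3 months, as a single contrast at two-sided 0.05.
- Take it from the planned mixed model with pre-operative strength as a covariate (its slope allowed to differ by visit), visit, group and group-by-visit, so that each group has its own mean at every visit.
- Label the day 2, day 5 and 12-month contrasts as secondary, as the outcomes section already does.
- State that the overall interaction test is not used for the primary objective.
- Name the response scale. The simplest match to the defined outcome is percentage change at each visit as the response. If Newtons are modelled instead, the outcome definition should be changed to agree.

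The cost is a few sentences, settled before unblinded analysis. The data, software and sample size stay the same.

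### The cut-off of more than three time points confines the mixed model to quadriceps strength; extending it to OKS, WOMAC and EQ-5D-5L would protect their 12-month comparisons against a small, conditional bias

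*Protocol article*

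**What the plan says.** All the relevant rules are in the protocol article, under Statistical analysis plan.

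- **Strength.** The mixed model is fixed for "quadriceps strength at the different follow-up time points (2 days, 5 days, 3 months and 12 months"), which is four follow-ups. One of its stated advantages is that "the method uses all available data even in the presence of unbalanced data".
- **Other continuous secondary outcomes.** The mixed model is to be considered for "continuous secondary outcomes that are available at multiple follow-up time points (> 3 time points"). Those "only assessed at baseline and once/twice at follow-up will be analysed using linear regression, allowing for estimation of clustered sandwich error estimates".
- **Missing data.** "Analysis will include cases with available data. No imputation of missing data will occur". The amount missing is to be described by group and by outcome.

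Table 1 and the section Outcome measures and assessment time points give OKS, WOMAC and EQ-5D-5L a baseline assessment and two follow-ups, at 3 and 12 months.

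**The concern.** The plan praises the mixed model for coping with unbalanced data, then sets an entry rule that no secondary outcome other than strength can meet. The outcomes it shuts out include the 12-month patient-reported scores, where some loss is to be expected. No reason is given for the cut-off, and there is no technical one: a likelihood-based mixed model can be fitted with two follow-ups.

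Clustered sandwich errors make the standard error valid for repeated measures on the same patient. They leave the point estimate as it is, so they do nothing about selective loss. When the regression estimates a separate group effect at each time, the 12-month contrast rests on patients who returned at 12 months. A patient with a 3-month score who is then lost does not inform it, even if that score predicts both the loss and the missing value. At stake is whether the 12-month comparisons of pain, function and quality of life describe everyone randomised or only those who responded.

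**Working it through.** **Step 1: which outcomes meet the rule.** Counts are from Table 1 and the outcome list.

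| Outcome | Follow-ups | Occasions including baseline | More than 3? |
|---|---|---|---|
| Quadriceps strength | 4 | 5 | yes |
| OKS, WOMAC, EQ-5D-5L | 2 | 3 | no |
| Knee Society Score | 1 in Table 1, 2 in the outcome list | 2 or 3 | no |
| Knee pain rating (days 2 and 5) | 2 | 2 (no baseline in Table 1) | no |
| Morphine equivalent dose ("mg, average for first 5 days") | 1 | 1 | no |

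Whether or not baseline is counted, no continuous outcome other than strength qualifies.

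**Step 2: the plan's sample size, for scale.** The inputs from Sample size are d = 0.65, two-sided alpha 0.05, power 80%, and 15% drop-out from 45 per arm.

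- Normal approximation: n = 2(1.960 + 0.842)²/0.65² = 15.70/0.4225 = 37.2, so 38 per arm.
- Noncentral t: power is 0.799 at 38 and 0.809 at 39. The stated 39 per arm is reproduced.
- Retained per arm: 45 × 0.85 = 38.25, taken as 38.
- Standard error of a group difference in SD units: √(2/38) = 0.229. With an assumed baseline correlation of 0.4: √[(2/38)(1 − 0.16)] = 0.210.

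**Step 3: when the difference is biased.** For arm k, let Δk be the mean 3-month score of those still observed at 12 months minus the mean of all in that arm. Let ρ be the correlation between 3 and 12 months. For normal scores with unit SD and loss that depends on the 3-month score:

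- bias of the 12-month mean in arm k = ρ × Δk
- bias of the unadjusted difference = ρ × (Δ1 − Δ2)

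The second is zero whenever Δ1 = Δ2. Score-dependent loss therefore always shifts the arm means, but it shifts the difference only if the arms lose patients differently or have different 3-month scores.

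**Step 4: size.** The following inputs are assumptions, not in the documents: ρ of 0.5 and 0.7, baseline correlation 0.4, loss log-odds changing by 1 per SD of the 3-month score, and all 15% lost after giving that score. Each scenario was simulated with 1,000,000 participants. The regression was 12-month score on group and baseline, in available cases. The likelihood estimate was b_group + b_3 × g. Here b_group and b_3 come from regressing the 12-month score on group, baseline and 3-month score in completers, and g is the baseline-adjusted 3-month group effect in everyone. This is what a mixed model with unstructured covariance delivers.

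| Loss mechanism | Size of baseline-adjusted bias, 15% loss (SD) | 30% loss (SD) |
|---|---|---|
| Same in both arms, no 3-month effect | 0.00 | 0.00 |
| Same in both arms, 3-month effect 0.3 to 0.65 SD | 0.01 to 0.03 | 0.01 to 0.05 |
| Depends on the score in one arm only | 0.05 to 0.08 | 0.09 to 0.14 |
| Opposite dependence in the two arms | 0.10 to 0.15 | 0.17 to 0.28 |

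The likelihood estimate stayed within 0.005 SD of the truth throughout. In the first row at 15% loss, the 12-month mean was shifted by 0.066 SD (ρ = 0.5) or 0.092 SD (ρ = 0.7). Both imply Δ of about 0.13 (0.066/0.5 = 0.132; 0.092/0.7 = 0.131), equal in the two arms, so the difference was unbiased, as step 3 predicts.

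**The case against.** The strongest reply is that the bias is small in the setting the documents describe. Participants and research staff are blinded (Blinding), and post-operative care follows the same pathways in both arms (Post-operative care and rehabilitation). Nothing suggests that loss would depend on the score differently by arm. Blinding does not exclude this, but the natural case is a shared mechanism, with bias of 0.03 SD or less. This stands.

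Three further points also stand.

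- The 15% is the drop-out allowance in the sample size for the 3-month primary outcome. Patients lost before 3 months have no 3-month score for any model to use. If half the 15% were lost after 3 months (an assumption), the same calculation gives at most about 0.02 SD under a shared mechanism and 0.03 to 0.045 SD if one arm's loss depends on the score.
- Patients who wish to withdraw are offered the questionnaires by mail, and up to four contact attempts are made. This should reduce loss on these very outcomes.
- The regression's terms are not spelled out. If one group effect were fitted across both follow-ups, the 3-month rows would contribute. The result would then be an average over time and not a 12-month contrast, so the concern applies when the contrast is estimated by group and time.

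A reader might infer that available-case regression is biased whenever 12-month loss depends on the 3-month result, or that it would understate a harmful tourniquet effect by a fifth or more. The documents support neither. The first needs the extra condition in step 3. The second needs arm-specific loss, and it also applies to a patient-reported score the d = 0.65 that the plan drew from electromyography for the strength outcome.

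The reply does not rescue the cut-off itself. It remains unexplained, and it withholds a method that the plan already uses and prefers for unbalanced data.

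**Conclusion.** The point holds in a limited form. The rule confines the mixed model to strength, and the 12-month comparisons of OKS, WOMAC and EQ-5D-5L are left to a method that can be biased when loss depends on the 3-month score and the arms differ in that score or in the loss mechanism. At 15% loss the bias is below one standard error (about 0.21 to 0.23 SD) in every scenario tried, and 0.03 SD or less unless the mechanism differs by arm. At 30% loss, only opposite dependence in the two arms can exceed one standard error. These sizes rest on assumed correlations and loss slopes.

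The primary outcome and the 3-month contrasts are not affected by 12-month loss. A reader might also infer a breach of the intention-to-treat statement. The plan says openly that it analyses available data, so this limits what the 12-month results represent and is not a contradiction. Severity is minor and confined to secondary outcomes.

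**What to change.** In the Statistical analysis plan section, change the threshold from more than three time points to two or more follow-up time points, and commit to the mixed model where the text now only considers it. Analyse OKS, WOMAC and EQ-5D-5L with the same restricted maximum likelihood model as strength: baseline, time, group, group-by-time and an unstructured covariance. Report the 3- and 12-month contrasts. Keep linear regression for outcomes with one follow-up, and retain the clustered regression as a sensitivity analysis for these scores.

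The new threshold would also take in the day 2 and day 5 pain ratings, where Table 1 gives no baseline term, and the Knee Society Score if its 12-month assessment is confirmed.

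The cost is a change of wording, with no new data. With baseline as a covariate, two follow-ups need only three covariance parameters (two variances and one correlation). The downside is reliance on the covariance model and on missingness at random given the observed scores. That assumption is weaker than the present one, because baseline-adjusted regression needs loss to be unrelated to the 12-month score given arm and baseline alone. Loss driven by a patient's unobserved later state would remain uncorrected under either method.

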## Background

Total knee replacement (TKR) is a common and successful procedure, with over 1 million TKRs occurring annually in OECD countries [1]. TKR is regularly performed using a tourniquet, with usage in 37–93% of surgeries [2, 3]. However, tourniquet use during TKR is debated due to evidence questioning the advantages, and the possibility of increased complications [4, 5].

A thigh tourniquet compresses the leg and restricts distal blood flow which is intended to reduce intra-operative blood loss at the surgical site. Tourniquet use has been suggested to improve surgical field view, allow cement to bond more effectively [6], and produce shorter operating time which might reduce the risk of infection [4]. A systematic review found tourniquet use reduced intra-operative blood loss (198 ml) and operating time (5 min), but did not affect post-operative blood loss or the possibility of requiring transfusion [4]. Tourniquet use increased the risk of thrombotic events such as deep vein thrombosis (DVT) and pulmonary embolism (PE) (risk ratio (RR) 5.00; 95% CI, 1.31 to 19.10), and non-thrombotic complications such as reoperation, haematoma, or nerve palsy (RR, 2.03; 95% CI, 1.12 to 3.67). Knee range of movement in the first 10 days post-operatively was 10.4 degrees less in the tourniquet group. More recently, Rathod et al. [7] found no difference in cement penetration when a tourniquet was used from incision to arthrotomy closure compared to using a tourniquet only during cementation. Pfitzner et al. [8] found cement mantle thickness was 1.2 mm (*p* = .009) greater in the tourniquet group than non-tourniquet group, and Ledin et al. [9] found no difference in prosthesis migration in tourniquet versus non-tourniquet TKR. Several investigators have reported higher post-operative pain when a tourniquet was used compared to no tourniquet [9–11].

Quadriceps function influences post-operative physical performance, functional ability and rehabilitation following TKR [12, 13]. Quadriceps dysfunction following TKR can be immediate, profound and persist for years after surgery, resulting in substantial functional deficits [14]. Mizner et al. [15] found quadriceps strength was 62% less than pre-operative values when measured four weeks after TKR.

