### Randomisation

People who meet eligibility requirements and provide informed consent will be randomly allocated to either tourniquet or non-tourniquet groups with a 1:1 allocation ratio in blocks of 10. The allocation sequence will be computer generated by the research coordinator prior to trial commencement. Allocation will be concealed until immediately prior to anaesthetic induction, at which time the surgeon will access the allocation code for that participant via an opaque sealed envelope.

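### No sparse-data method is named for rare binary secondary outcomes: standard logistic regression gives no finite odds ratio if one arm of about 45 has no events

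*Protocol article*

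**What the plan says.** In the protocol article, the Statistical analysis plan section covers every categorical secondary outcome in one sentence: "Secondary outcomes that are categorical will be analysed using logistic regression models". It does not state the estimation method, the effect measure or the type of interval, or whether complications are modelled by type or pooled. In the same section, quantile regression is the alternative if linear-model assumptions fail, and negative binomial or similar models are the alternative to Poisson. No alternative is given for binary data. Categorical data will also be summarised as frequencies and percentages.

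The section on outcome measures lists the outcomes concerned (list items run together in the extracted text): "Complications during inpatient stayDVT or PEWound complications such as infection, haematoma or breakdown", then medical emergency calls or death, and separately revision within 12 months.

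The Sample size section bases the trial on quadriceps strength alone: "allowing for a medium to large effect size (Cohen’s d = 0.65"), and "a two-sided significance level of α = .05 and power of 80%, a minimum sample size of 39 participants per arm was estimated". It continues: "Allowing for a 15% drop-out rate, we aimed to recruit 45 participants to each group". The Background section reports, from a systematic review, a relative effect of tourniquet use on thrombotic events of "risk ratio (RR) 5.00; 95% CI, 1.31 to 19.10". It gives no absolute rate.

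**The concern.** Complications, including revision, are a named secondary objective, and the Background presents thrombotic harm as a reason why tourniquet use is debated. These events may be few in a trial of this size.

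When one arm has no events, the logistic likelihood keeps rising as the treatment coefficient moves towards infinity. Software then either drops the term or prints a very large coefficient with a far larger standard error. The Wald p-value is close to 1 even when all the events fall in one arm and an exact test would be significant at the plan's two-sided 0.05 level. Events only in the tourniquet arm are the pattern that a harm comparison should detect. If the plan names no method for that case, one would be chosen after the empty cell has been seen.

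**Working it through.** **Arm size.** A two-sample t-test with d = 0.65, two-sided α = 0.05 and 80% power needs 39 per arm (power 0.799 at 38 and 0.809 at 39), which reproduces the stated figure. For drop-out, 39 × 1.15 = 44.85, which rounds up to the stated 45. Dividing instead, 39/0.85 = 45.9, gives 46, a difference that does not matter here. I use n = 45 for inpatient outcomes and n = 39 as the lower figure for 12-month revision.

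**What happens with an empty arm.**
- 2/45 against 0/45: the maximum-likelihood fit did not converge. It stopped at a log odds ratio of 19.1 with a standard error of about 9,597. These values depend on the software; the true maximum is at infinity.
- 6/45 against 0/45: Wald p = 0.999. Fisher's exact two-sided p = 2 × C(45,6)/C(90,6) = 2 × 8,145,060/622,614,630 = 0.026.
- 7/45 against 0/45: Wald p = 0.999, Fisher p = 0.012.

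**How often an arm is empty.** With risks p0 (no tourniquet) and p1 (tourniquet):
- P(at least one empty arm) = 1 − [1 − (1 − p0)^n][1 − (1 − p1)^n]
- P(events only in the tourniquet arm) = (1 − p0)^n × [1 − (1 − p1)^n]

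The documents give no absolute rates, so every risk below is an assumption.

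*Equal risks in both arms:*

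| Risk | At least one empty arm, n = 45 | Same, n = 39 | Both arms empty, n = 45 | Tourniquet-only events, n = 45 |
|---|---|---|---|---|
| 1% | 87% | 90% | 40% | 23% |
| 2% | 64% | 70% | 16% | 24% |
| 3% | 44% | 52% | 6% | 19% |
| 5% | 19% | 25% | 1% | 9% |
| 10% | 2% | 3% | <0.1% | 1% |

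Example at 2%, n = 45: 0.98^45 = 0.403, and 1 − (1 − 0.403)² = 0.643.

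The probability reaches one half where (1 − p)^n = 1 − √0.5 = 0.293. That is p = 2.7% for n = 45 and 3.1% for n = 39.

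*Risk ratio 5.00 from the Background, n = 45:*

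| Assumed control risk | Tourniquet risk | At least one empty arm | Tourniquet-only events |
|---|---|---|---|
| 0.5% | 2.5% | 86% | 54% |
| 1% | 5% | 67% | 57% |
| 2% | 10% | 41% | 40% |

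Example at 1%: 0.99^45 = 0.636 and 0.95^45 = 0.099. So 1 − (0.364 × 0.901) = 0.672, and 0.636 × 0.901 = 0.573.

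**The case against.** The strongest reply is that the article says only logistic regression. A reader might infer that ordinary maximum likelihood is fixed and that an odds ratio with a Wald interval is the planned result. The text says neither. Exact and Firth-penalised logistic regression both fit its sentence, and a separate analysis plan could name one. This stands as a limit on the wording. It does not remove the point: the section sets out fallbacks for the other two model families, and unqualified logistic regression is normally read as maximum likelihood.

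Three other stronger readings should also be resisted.

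- **That an empty arm is likely.** This depends on rates that the documents do not give. At 5% per arm the chance is 19%, and at 10% it is 2%. Wound complications or emergency calls might be that common, and pooling complication types would reduce the problem further. Where both arms are empty (40% at an equal risk of 1%), no method gives an informative comparison.
- **That estimates from very few events are strongly biased away from the null.** Exact enumeration at n = 45 and risk ratio 5.00, restricted to finite estimates, shows the opposite. The mean log odds ratio is 0.33 against a true 1.63 (control risk 0.5%), 0.65 against 1.65 (1%) and 1.16 against 1.69 (2%). Under equal risks the mean is 0.
- **That no usable inference survives.** With one empty arm, a likelihood-ratio test and a one-sided profile limit still exist. For 4/45 against 0/45 the lower profile limit for the odds ratio is about 1.7. For 6/45 against 0/45 the likelihood-ratio statistic is 2[6 ln(6/45) + 39 ln(39/45) − 6 ln(6/90) − 84 ln(84/90)] = 8.75, p = 0.003. The failures are confined to the point estimate, the upper limit and Wald inference.

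Counts and percentages are already planned, so the raw data would be visible. They do not supply an interval or a test.

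**Conclusion.** The point holds in conditional form. For DVT or PE, for revision, and for other complications if they are uncommon and modelled by type, the named method has no finite odds ratio and no useful Wald test when one arm is empty. No sparse-data alternative is stated. At 45 per arm, an empty arm is at least as likely as not if the risk is about 2.7% or lower in both arms. Under the quoted risk ratio, that crossover lies at a control risk between 1% and 2%. All of these frequencies rest on assumed rates.

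The primary outcome and the sample size are unaffected. The change is worth making because the exposed comparisons are the safety ones, and because the method should be chosen before any empty cell is seen.

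**What to change.** Add a sentence to the analysis plan before unblinding. For binary complications and revision with few or no events in either arm, report the counts and the risk difference with an exact or score 95% interval and Fisher's exact test. If a model is wanted, use Firth-penalised or exact logistic regression. Keep standard logistic regression where both arms have adequate events. State in advance the event count that triggers the switch, and say whether complications are analysed by type, pooled or both.

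The cost is small. Stata and R, the two packages named, both support these methods, and no data collection or clinical procedure changes. Exact tests are slightly conservative: 5/45 against 0/45 gives 2 × C(45,5)/C(90,5) = 2 × 1,221,759/43,949,268 = 0.056, so six events against none is the first such pattern to pass 0.05.
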